# IX. STUDY WITHDRAWAL

### A. Early termination of therapy

Patients will have their study therapy withdrawn if any of the following events occur:

i) withdrawal of consent to participate.

ii) termination of the study.

iii) pregnancy.

iv) a medically significant, grade IV toxicity occurs that is attributable to study therapy.

v) the patient experiences dose-limiting toxicities at the minimal permissible dose for this protocol (1.5 MIU q12h for 5 days every eight weeks).

vi) any event, other than those allowed that delays the commencement of an IL-2 treatment cycle by more than eight weeks.

vii) malignancy requiring systemic therapy.

viii) patient non-compliance.

ix) the principal investigator believes it is in the best interests of the patient.

# X. TRIAL MANAGEMENT

### A. DATA SAFETY MONITORING BOARD

An independent Data Safety Monitoring Board (DSMB) will be established to review the conduct of this study. The DSMB will be asked to address specific questions relevant to the conduct of the trial. The DSMB will make recommendations regarding further progress for the study.

### B. ENDPOINT REVIEW COMMITTEE

An independent Endpoint Review Committee (ERC) will be established to review all diagnostic information provided by participating sites for trial patients who are believed to have had clinical disease. Only those endpoints described as fulfilling all necessary diagnostic criteria by the ERC will be included in the analyses of clinical efficacy. A listing of acceptable definitive and presumptive diagnostic criteria for AIDS-defining illnesses is given in appendix I.

### C. NATIONAL STEERING COMMITTEE

Where appropriate a National Steering Committee will be established. Regular communication within a participant territory will be facilitated by the establishment of a National Steering Committee (NSC). This will include the principal investigator from each site (or their deputy) along with representatives of the IND Sponsors or their agent. This committee will also establish policy for the publication of trial data.

### D. INTERNATIONAL STEERING COMMITTEE

Overall management of the study will be undertaken by the International Steering Committee (ISC). This group will comprise representatives selected from each of the NSC together with representatives from the IND Sponsors. As required the group may also seek the input of *ad hoc* members. This committee will also establish policy for the publication of trial data.

# XI. ADVERSE EVENTS AND MANAGEMENT

### A. ADVERSE EVENT DEFINITION

All adverse events, regardless of severity or relationship to study product, must be recorded in the case report form.An adverse event is any undesired, noxious or pathological change in a patient as indicated by physical signs, symptoms and/or laboratory changes that occurs in association with the use of study drug regardless of the relationship to study drug. This definition includes intercurrent illness or injury, as well as exacerbation of pre-existing conditions, and clinically significant changes in laboratory test results (those that required a change in study therapy). All adverse events should be followed until a final outcome can be achieved, be this resolution or determination that the sequelae are considered chronic. Laboratory abnormalities or changes in weight, Karnofsky Performance Status, or vital signs that are not associated with medical interventions should not be recorded in the adverse event pages. Similarly, conditions/abnormalities arising from infectious origin or from progression of HIV disease (excluding the development of neoplasia) should not be recorded on the adverse pages.

**Please refer to the toxicity grading scale, Appendix D, when assessing the severity of adverse events. Please note, this scale serves as a guide and should be used in association with the patientÕs clinical presentation in any assessment of severity.**

Where a diagnosis is possible it is preferable to report this rather than a series of individual terms each related to the same diagnosis. When reporting a syndrome, indicate the associated signs and symptoms parenthetically following the syndrome rather than as separate events.

Safety will be assessed in all patients enrolled on the study during the treatment period and through the post-treatment evaluation. Any unresolved adverse events or toxicities will be followed until they resolve or until they are determined to be chronic. Any serious adverse events or toxicities that occur during therapy or in 6 months following completion of IL-2 therapy must be reported to the IND Sponsors immediately.

The definition of a serious adverse event is as follows:

A Serious Adverse Event (SAE) means any experience that suggests a significant hazard, contraindication, side effect or precaution. In that regard, medical judgment is required in the evaluation of incoming information. As a rule, a serious adverse event includes any event that is fatal or life-threatening, is permanently disabling, requires or prolongs inpatient hospitalization, is a congenital abnormality in a newborn or requires intervention to prevent permanent impairment or damage. Therefore, the following must be reported:

1. Death

2. Life-threatening illness

3. Hospitalization (initial or prolonged)

4. Disability (results in a significant, persistent, or permanent change, impairment, damage or disruption in the patientÕs body function/structure, physical activities or quality of life)

5. Congenital anomaly in a newborn following treatment during pregnancy

6. Requires intervention to prevent permanent impairment or damage (a condition which requires medical or surgical intervention to preclude permanent impairment or damage to the patient)

7. Occurrence of malignancy

8. Accidental or intentional overdose with sequelae

9. A grade IV toxicity

Any serious adverse event, whether or not considered related to study medication must be reported as soon as possible to the Division of AIDS (DAIDS).

The patient should be followed carefully until the condition has resolved and/or etiology has been identified. Any medication taken to relieve symptoms of the medical problem and the outcome of the event will be recorded.

The Investigator is responsible for informing the IRB as soon as possible, but in no event later than 10 working days after the discovery of death from any cause, or after the discovery of any serious adverse events or problems of clinical significance that may reasonably be regarded as caused or associated with the study product.

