# I. SYNOPSIS

This protocol describes a randomized, phase II study of subcutaneous interleukin-2 (IL-2) therapy in HIV disease. There are three primary objectives:

1. to demonstrate the safety and tolerance of IL-2 in the absence of concomittant antiretrovirals.

2. to demonstrate the immunological efficacy of IL-2 in the absence of concomittant antiretroviral therapy as defined by increases of CD4+ cell counts from baseline.

3. To assess the effects of IL-2 in the absence of concomittant antiretroviral therapy on plasma HIV RNA levels as defined by changes from baseline.

Approximately 36 patients with HIV infection, > 350 CD4+ cells/mm3 and no history of opportunistic infection will be required to complete the trial. Individuals never previously treated with antiretrovirals will be eligible to participate. Eligible patients will be randomly assigned to receive one of two treatment regimens:

A. No therapy (n=12)

B. Subcutaneous IL-2 at one of 2 doses, q12h x 5 days every 8 weeks (n=24)

Two different dose levels of IL-2 will be studied. The first group will receive 4.5 million units (MIU) q12h x 5 days every eight weeks. The second group will receive 7.5 MIU q12h x 5 days every eight weeks. Following the completion of this study, continued treatment for all patients will be made available through an additional protocol that will be based upon the results of the current study. It is anticipated that this additional study will be a phase III trial involving a total of 3700 patients worldwide.

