### A. INTERLEUKIN-2 IN HIV DISEASE

Interleukin-2 is a 15Kdalton, immunostimulatory protein produced in vivo by T-lymphocytes following activation by antigens. It is central to the appropriate responsiveness of the immune system challenged by invading pathogens. Its synthesis and release by CD4+ T-lymphocytes in particular, is of critical importance to the orchestrated events that follow detection of foreign antigen and lead to clearance of pathogen and resolution of disease. IL-2 results in the proliferation and maturation of both T- and B- lymphocytes (Smith, 1988). In vitro, exogenous IL-2 can enhance the NK and CTL activity of lymphocytes from patients with AIDS (Rook et al, 1985).

Immunotherapy of HIV disease with IL-2 has undergone considerable investigation in Phase I and II trials. These studies have defined the safety profile of IL-2 delivered in a number of different regimens as well as the virological and immunological changes resulting from treatment.

Initial Phase I studies were conducted in AIDS patients with KaposiÕs sarcoma. Purified, native IL-2 was administered by continuous intravenous infusion (CIV) for 5 days a week for four consecutive weeks at doses ranging from 250 to 250,000 units per day (Lane et al, 1984). In a second group of 21 patients recombinant IL-2 was administered by CIV for 5 days every eight weeks at doses ranging from 1,500 Units to 12.5 MIU per day (Murphy et al, 1988). In these studies toxicities were minimal and included hepatic dysfunction, febrile illness, eosinophilia, mild prolongation of PTT and proteinuria. There was an increase in the incidence of bacterial infections compared with patients receiving g-interferon. Although treatment did not result in consistent clinical responses in patients with late-stage HIV disease, there was a consistent increase (up to five-fold) in circulating lymphocyte counts.

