Twice daily SC dosing for 5 days of a four-week cycle has been evaluated in a five-arm Phase II trial conducted by community-based practitioners and sponsored by Applied Immune Sciences (AIS, Santa Clara, California). Patients in this trial were randomized to receive either 2MIU m2/dose (low dose) or 4 MIU m2/dose (high dose), twice daily with or without ex vivo expanded CD8+ T-lymphocytes for a total of 5 cycles (Deresinski et al, 1995). A total of 23 patients received IL-2 alone under this protocol. The study was controlled with a treatment arm of antiretroviral therapy alone. Toxicities from this trial were relatively mild and related to flu-like symptoms common to nearly all IL-2 regimens. One asplenic patient died following pneumococcal sepsis one week after completion of therapy. The contribution of IL-2 to this even is not known. Transient increases in HIV virus load were noted at day 5 of therapy (2-3 fold increases), although upon completion of study, levels of plasma HIV-RNA were not significantly greater than baseline levels. Recipients of low-dose IL-2 had a mean increase in CD4+ cell count of 34% (range -27 to 93) and recipients of high dose IL-2 had a mean increase of 38% (range -28 to 112). The absence of a dose response is thought to reflect the extent of dose reductions undertaken in the high-dose recipients. Increments in CD4+ cell count were seen in patients with CD4+ cell counts both above and below 350 cells/mm3 suggesting that a subcutaneous regimen might be applicable for patients with more advanced HIV disease.

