**Table 4**

**ANTIRETROVIRAL TREATED PATIENTS**

| Test/assessment/  sample | Week 0(1) | Week 8 (1) | Week 16 (1) | Week 24 (1) |
| --- | --- | --- | --- | --- |
|  |  |  |  |  |
| Vital signs/weight | X | X | X | X |
| History (2) | X | X | X | X |
| CBC/differential | X | X | X | X |
| Serum chemistries | X | X | X | X |
| Flow cytometry | X | X | X | X |
| Plasma virology | X | X | X | X |
| Whole Blood for PBMC | X | X | X | X |
| Pregnancy test- women only | X |  |  |  |

(1) These visits may take place ± 3 weeks

(2) Update treatment history; verification that no important events occurred

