**Signs or symptoms which require physician evaluation include (but are not limited to):**

- Urine output <500 cc/day
- Fever >102 which does not respond to antipyretics. Because IL-2 adds a neutrophil defect to the immune defect of the HIV seropositive patient, any suggestion of infection must be evaluated aggressively. Patients should have blood and other sites cultured as clinically indicated. It is important to note that the neutrophil defect associated with IL-2 treatment persists for at least one week following IL-2 completion.
- Pain or induration at subcutaneous injection site.
- Greater than mild anxiety or agitation; any signs of confusion, somnolence or disorientation; neurotoxicity from IL-2 is often progressive even when the IL-2 infusion has been discontinued.
- Respiratory rate of >25 or shortness of breath unassociated with fever
- Institutional norms should be considered in determining whether oral or intravenous supplementation of Ca++, Mg++, or PO4 is appropriate

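### Section XI.A contradicts itself on recording infections and HIV progression, and adverse events are collected unequally in IL-2 and control patients

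*Protocol*

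**What the plan says.** The Synopsis gives as its first primary objective "to demonstrate the safety and tolerance of IL-2 in the absence of concomittant antiretrovirals". Section V.A frames safety and tolerability, with efficacy, as a comparison with no therapy.

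Section XI.A opens with a general rule: "All adverse events, regardless of severity or relationship to study product, must be recorded in the case report form". It adds: "This definition includes intercurrent illness or injury, as well as exacerbation of pre-existing conditions". Later in the same paragraph it says that "conditions/abnormalities arising from infectious origin or from progression of HIV disease (excluding the development of neoplasia) should not be recorded on the adverse pages". The definition itself describes an event occurring while study drug is used, whether or not the drug caused it. The section also promises that safety will be assessed in all enrolled patients, through the post-treatment evaluation.

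Table 3, for IL-2 patients, has a toxicity and adverse event row on days 1 to 5, day 8 (first cycle only) and day 29, with diary cards kept throughout. Table 4, the control schedule, has no such row and no diary. It has a History item at weeks 0, 8, 16 and 24, explained as "Update treatment history; verification that no important events occurred", and visits may move by three weeks either way.

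On infection risk, section II.A says of the early IL-2 studies: "There was an increase in the incidence of bacterial infections compared with patients receiving g-interferon". Section II.B reports: "One asplenic patient died following pneumococcal sepsis one week after completion of therapy". Appendix F warns that "the neutrophil defect associated with IL-2 treatment persists for at least one week following IL-2 completion".

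**The concern.** A site cannot follow both the general rule and the exclusion in section XI.A, and different sites may resolve the conflict differently. If the exclusion is followed, a class of event that the protocol itself treats as a reason for vigilance stays off the adverse event pages. Data that were never collected cannot be recovered at the analysis stage.

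The second problem is comparability. Section VIII.E.3 summarises safety by treatment received. If one arm is questioned daily during dosing and keeps a diary, and the other is asked at eight-week visits whether anything important happened, a difference in event rates partly reflects how hard each arm was looked at. The definition tied to study drug makes this worse, because a strict reader could conclude that an untreated control cannot have an adverse event.

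The two defects do not pull in the same direction. The exclusion hides infections in either arm. The unequal collection tends to inflate recorded events in the IL-2 arms relative to control.

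**Working it through.** The protocol gives no figure on this point, so the check is mainly a comparison of texts.

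**1. The conflict.** An ordinary bacterial infection during follow-up is an intercurrent illness. Under the first two statements in section XI.A it is an adverse event and must be recorded. Under the third it must not go on the adverse event pages. Sections VII.C.1 and XI.B and Appendix D repeat the all-events rule without mentioning the exclusion.

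**2. Which events have another route.**

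| Event | Route other than the adverse event pages |
| --- | --- |
| Infection that is fatal, life-threatening, leads to hospitalisation or is grade IV | SAE reporting, section XI.A, whether or not related |
| AIDS-type diagnosis listed in Appendix I | Endpoint Review Committee, section X.B |
| Non-serious bacterial infection | None described |
| Non-serious progression event outside Appendix I | None described |

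Apart from the mycobacterial entries, the only bacterial diagnosis in Appendix I is Salmonella septicaemia. Recurrent pneumonia and wasting syndrome are AIDS conditions in Appendix B but do not appear in Appendix I. Oral thrush, in category B of Appendix B, is also absent. The committee's output feeds analyses of clinical efficacy, not the safety summary, and section VIII.E.1 names no clinical efficacy endpoint.

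**3. Scheduled collection over three cycles.**

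- IL-2 patients: days 1 to 5 and day 29 give 5 + 1 = 6 assessments per cycle. With day 8 in cycle 1 only, the total is 3 × 6 + 1 = 19, plus diary cards.
- Controls: History at weeks 8, 16 and 24 gives 3 checks after week 0, with no diary.

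Table 5, which applies to everyone, has a physical examination but no adverse event row.

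**4. Possible size of the gap.** The documents give no infection rate, so this step rests on assumptions. Let p be the proportion of IL-2 patients with an infection, assumed 10–30%. Let s be the share of those whose infection is serious, assumed 10–50%. Each patient is classified by the worst infection. Table 2 allocates 12 + 12 = 24 patients to IL-2.

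- Patients with infection: 24 × p = 2.4 to 7.2.
- Seen through SAE reporting: 24 × p × s = 24 × 0.10 × 0.10 = 0.24, to 24 × 0.30 × 0.50 = 3.6.
- Not on the adverse event pages and not an SAE: 24 × p × (1 − s) = 24 × 0.10 × 0.50 = 1.2, to 24 × 0.30 × 0.90 = 6.5.

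The missing share is 1 − s, or 50–90% of infected patients. It is an upper limit for full loss, because some non-serious infections may be Appendix I diagnoses.

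**The case against.** The strongest reply is that the protocol has several safety nets. SAE reporting covers infections with no exemption, so a death from sepsis such as the one in section II.B would be captured. Appendix I diagnoses go to an independent committee. Biological progression is followed in both arms through CD4+ count and plasma HIV-RNA, the primary endpoints. The exclusion refers to the adverse event pages, and the case report form is not shown, so infections might be recorded on another page. All of this stands, and it limits the gap to non-serious infections and to clinical progression outside Appendix I. It does not remove the contradiction, and no alternative page is mentioned.

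Three stronger readings are tempting, and the documents do not support them.

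- A reader might infer that controls have no safety assessment. They have the History check at four visits, vital signs, blood counts and chemistries. They also have the post-therapy examination and fall under the promise to assess all enrolled patients. Their collection is less structured, not absent.
- A reader might infer that IL-2's main harms go uncollected. The dose-limiting toxicities listed in section II.A, such as raised creatinine, liver test changes, cytopenias, gastrointestinal symptoms and fever, are not excluded and fall within the Table 3 assessments.
- A reader might infer that the protocol blames IL-2 for infections. Section II.A reports an increase against interferon recipients in early infusion studies. Section II.B says that IL-2's contribution to the sepsis death is not known. Only the neutrophil defect is attributed to IL-2.

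**Conclusion.** The text is wrong as written and should be corrected, though the gap is narrower than the exclusion sentence alone suggests. Section XI.A gives incompatible instructions on infections and HIV progression, and its definition of an adverse event does not fit an untreated control. Followed literally, it leaves non-serious infections, and non-serious progression events outside Appendix I, off the adverse event pages.

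Under the assumed ranges, this could affect about 1 to 6 of the 24 IL-2 patients. That range illustrates scale and is not an estimate from the documents. The conclusion does not depend on it; it rests on the wording and on the difference between Tables 3 and 4. With 19 scheduled assessments and a diary on one side and three history checks on the other, a comparison of event rates with no therapy would be biased even with complete reporting of what was found.

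**What to change.** 1. In section XI.A, remove the sentence that excludes conditions of infectious origin or HIV progression. Record these as adverse events, with a flag for suspected HIV progression so that they can be shown separately.
2. Define adverse events from randomisation in all patients, without reference to use of study drug.
3. Add the toxicity and adverse event row of Table 3 to Table 4 at weeks 8, 16 and 24. This reduces the asymmetry but does not remove it, because daily assessment during dosing and diary cards remain in the IL-2 arms only. The report of the arm comparison should say so.

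The cost is a change of protocol wording, one extra row at control visits that already take place, and slightly more adverse event data entry. Treatment is not affected.

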### B. DEFINITION OF DOSE-LIMITING ADVERSE EVENT

A medically significant, dose-limiting adverse event will be defined as one which is dose-limiting for a monitored outpatient regimen. All adverse events which are regarded as dose-limiting will be clearly identified in the case report forms. All adverse events will be recorded on case report forms regardless of the assessment of their relation to the drug. **The study monitor must be notified of each dose-limiting adverse event.**

### C. OVERDOSE

In the event the patient receives more IL-2 than the established dosing regimen for a cycle, the study monitor will be notified immediately.

# XII. INSTITUTIONAL REVIEW BOARD APPROVAL/ETHICS COMMITTEE ACCEPTANCE

The principal Investigator agrees to provide the Institutional Review Board (IRB)/Ethics Committee (EC) with all appropriate material including the Informed Consent document. The trial will not be initiated until appropriate IRB/EC approval of the protocol and the Informed Consent document have been obtained in writing by the Investigator and copies have been received by the IND Sponsors. Appropriate reports on the progress of the study by the principal Investigator will be made to the IRB/EC and the IND Sponsors in accordance with applicable government regulations and in agreement with policy established by the IND Sponsors.

# XIII. INFORMED CONSENT

A properly executed written informed consent, in compliance with 21 CFR 50 (see appendix J) as far as is possible within the territory in which the protocol is active, shall be obtained from each patient prior to entering the patient into the trial or prior to performing any unusual or non-routine procedure that involves risk to the patient. If the patient is unable to give consent, he/she may not be entered to the study. A copy of the informed consent document to be used will be submitted by the Investigator to the Institutional Review Board/Ethics Committee (IRB/EC) for review and approval prior to the start of the study. The Investigator shall provide a copy of the signed informed consent to the patient and a copy shall be maintained in the patientÕs record file. Attention is directed to the basic elements that are required to be incorporated into the informed consent under U.S. Federal Regulations for Protection of Human Subjects (21 CFR 50.25[a]). Additional elements of informed consent, if appropriate, must be included in the informed consent document (21 CFR 50.25[b]).

Before initiation of the study, the Investigator must provide the IND Sponsors with a copy of the IRB/EC approved consent form.

